## Abstract

**Background:**

Excess dietary salt consumption is a major contributor to hypertension and cardiovascular disease. Public education programs on the dangers of high salt intake, and population level interventions to reduce the salt content in foods are possible strategies to address this problem. In Jamaica, there are limited data on the levels of salt consumption and the population’s knowledge and practices with regards to salt consumption. This study therefore aims to obtain baseline data on salt consumption, salt content in foods sold in restaurants, and evaluate knowledge, attitudes, and practices of Jamaicans regarding salt consumption.

**Methods:**

The study is divided into four components. Component 1 will be a secondary analysis of data on urinary sodium from spot urine samples collected as part of a national survey, the Jamaica Health and Lifestyle Survey 2016-2017. Component 2 will be a survey of chain and non-chain restaurants in Jamaica, to estimate the sodium content of foods sold in restaurants. Component 3 is another national survey, this time on a sample 1,200 individuals to obtain data on knowledge, attitudes and practices regarding salt consumption and estimation of urinary sodium excretion. Component 4 is a validation study to assess the level of agreement between spot urine sodium estimates and 24-hour urinary sodium from 120 individuals from Component 3.

**Discussion:**

This study will provide important baseline data on salt consumption in Jamaica and will fulfil the first components of the World Health Organization SHAKE Technical Package for Salt Reduction. The findings will serve as a guide to Jamaica’s Ministry of Health and Wellness in the development of a national salt reduction program. Findings will also inform interventions to promote individual and population level sodium reduction strategies as the country seeks to achieve the national target of a 30% reduction in salt consumption by 2025.

## Introduction

High blood pressure is the leading risk factor for the global burden of disease and is responsible for over nine million deaths worldwide each year.
^
1
^
^,^
^
2
^ In Jamaica, data from the Jamaica Health and Lifestyle Survey 2016-2017 (JHLS-III) showed that two-thirds of the population have an abnormally high blood pressure; approximately one third (33.8%) had hypertension (more than 140/90 mmHg) and 34.0% had prehypertension (120-139 mmHg systolic or 80-89 mmHg diastolic) using the JNC-7 classification.
^
3
^ Data from the Statistical Institute of Jamaica (STATIN) revealed that cardiovascular disease (CVD) was responsible for almost 6,000 deaths in 2016, representing 32% of all deaths.
^
4
^ Given the high burden of hypertension and the fact that hypertension is responsible for approximately 50% of CVD deaths,
^
5
^ it is imperative that the Jamaican public be aware of the adverse effects of hypertension and its risk factors. In addition, Jamaica’s public health agencies and non-governmental organizations working in the health sector have a responsibility to implement programs to mitigate the impact of elevated blood pressure on population health.

There are many factors that contribute to the burden of hypertension, including salt consumption, obesity, insulin resistance, psychosocial stress, and genetic predisposition. There are also associations with smoking and harmful use of alcohol. Reducing dietary salt consumption, reducing obesity, smoking cessation, and avoiding harmful use of alcohol are among the strategies that can be implemented to reduce hypertension and CVD at the population level.

At present, there is strong evidence to support the potential impact of dietary salt reduction in the general population as a strategy for the reduction of hypertension and CVD.
^
6
^
^–^
^
12
^ For example, the United Kingdom (UK) developed and successfully implemented a program of voluntary salt reduction in collaboration with the food industry in the early 2000s, in which mean population salt intake was reduced by 15%, from 9.5 g daily in 2003 to 8.1 g daily in 2011.
^
8
^
^,^
^
9
^ Over the same period, there was a corresponding reduction in population mean systolic blood pressure (SBP) of 2.7 mmHg after adjusting for potential confounding factors.
^
8
^
^,^
^
9
^ Stroke and ischemic heart disease (IHD) mortality were reduced by 36% over the same period; it was estimated that approximately 30% of the reduction in stroke and 20% of the reduction in IHD were attributable to the reduction in salt intake.
^
8
^

The population approach as a strategy to achieve sodium reduction is supported by recommendations from the World Health Organization (WHO) and Pan American Health Organization (PAHO).
^
2
^
^,^
^
13
^ Key components of the strategy recommended by WHO and PAHO include public education programs, standardized food labelling, gradual reduction of salt content in processed foods and national surveillance systems to identify salt intake levels and major sources of salt intake. It is widely believed that population-based approaches are required to achieve the desired salt reduction, as most dietary salt consumption comes from processed foods and foods prepared outside the home, rather than by adding salt at the table.
^
2
^
^,^
^
13
^

In addition to the population-based strategies mentioned above, several studies have shown that individual-level and community-based interventions, including salt substitution, education on salt reduction strategies, use of digital platforms and electronic education materials are effective in reducing blood pressure and cardiovascular disease.
^
14
^
^–^
^
17
^ Of note, Aliasgharzadeh
*et al*. found that multicomponent interventions may be more effective than single component interventions.
^
16
^

Measurement of sodium intake in populations is challenging. Measures include dietary assessment and measurement of urinary sodium excretion.
^
18
^ Dietary sodium assessment requires significant time commitments, often underestimates sodium consumption, and is considered by some to be unsuitable for measuring population sodium intake.
^
18
^ Currently, 24-hour urinary sodium excretion is considered the gold standard method for assessment of sodium consumption.
^
18
^
^–^
^
20
^ This procedure is appropriate, given that approximately 90% of consumed sodium is excreted in the urine.
^
18
^ The 24-hour urine collection is still challenging to accomplish in large population-based studies, resulting in some studies estimating 24-hour urine excretion from a spot urine specimen.
^
18
^
^–^
^
20
^ A number of formulae have been published for estimating 24 hour urine sodium excretion from spot urine specimens, including the Tanaka formula,
^
21
^ the Kawasaki formula
^
22
^ the INTERSALT formula,
^
23
^ and the PAHO formula.
^
13
^ A recent systematic review and meta-analysis found that estimates of mean population sodium intake from spot urine samples can provide a good indication of overall population salt intake with excellent sensitivity and specificity.
^
20
^

Globally, salt consumption is much higher than recommended. In 2010, global mean sodium intake was 3.95 g/day, with intake in men being approximately 10% higher than in women.
^
24
^ Intakes were highest in East Asia, Central Asia and Eastern Europe and lowest in sub-Saharan Africa and Latin America.
^
24
^ In the United States mean sodium intake was approximately 3.6 g/day and exceeded the recommended daily intake of 2.3 g/day for all age groups except for those 2-3 years old.
^
25
^ Data from the Health of the Nation Study in Barbados showed that mean sodium intake was 2.7 g/day, with intakes higher in men and young people.
^
26
^ Approximately 67% of individuals exceeded the WHO recommended limit of 2.0 g/day.
^
26
^

There are very little data on salt consumption patterns among Jamaicans, but it is generally believed that salt consumption is high. This is due to frequent consumption of salted meats (
*e.g.*, salt fish, salt mackerel, salted pork) in popular local dishes, frequent consumption of canned foods (such as corned beef), and frequent intake of fast foods, which are often high in salt content. Data from the 1990s provide some evidence for high salt consumption in Jamaica. In the Sodium Reduction Trial (SORT), baseline sodium excretion was found to be 149 mEq/day (3,437 mg/day) among a sample of 56 patients.
^
27
^ Additionally, the Spanish Cohort Study reported estimated sodium excretion of 3.3 g/24 hour,
^
28
^ but no recent or national estimates are available. More recently, data from JHLS-III found that among urban participants only 52% were classified as having a low salt diet, defined as no added salt at the table and infrequent consumption of processed foods.
^
29
^

In keeping with the recommendations of WHO and PAHO and consistent with Caribbean Community (CARICOM) recommendations and a mandate of the Ministry of Health and Wellness in Jamaica, we propose the implementation of a national salt reduction program in order to reduce blood pressure and associated CVD. The program will be aligned with the overall Ministry of Health’s National Strategic and Action Plan for Prevention and Control of Non-Communicable Diseases (NCDs) and the mandate of the Food Industry Task Force. Implementation of a national salt reduction program and achieving the desired effect of reduced blood pressure and associated CVD will require a sequence of actions including the steps included in the WHO SHAKE Technical Package for Salt reduction Program. These strategies include: (i) “measure and monitor salt intake” in the population; (ii) “promote reformulation of foods and meals to contain less salt”; (iii) “implement standards for effective and accurate labelling and marketing of food”; (iv) “educate and communicate to empower individuals to eat less salt”; and (v) creating “support settings to promote healthy eating”.
^
2
^

Jamaica has adopted the global target set by WHO to reduce salt consumption by 30% by 2025. However, Jamaica does not have any baseline data on current salt consumption and therefore would be unable to indicate whether these targets are being met. Additionally, Jamaica does not any available data on salt content in restaurant foods, but a previous study had collected data on sodium content in packaged foods.
^
30
^

The objectives of this study are as follows:
1.
**Objective 1:** To estimate dietary sodium consumption among Jamaicans using spot urinary sodium analyses.2.
**Objective 2:** To assess the use of sodium in the preparation of restaurant foods and estimate the sodium content in restaurant foods.3.
**Objective 3:** To conduct a baseline survey on current knowledge, attitudes, and practices regarding salt intake in Jamaica, and estimate current levels of salt consumption. We will also evaluate associations between knowledge and attitudes regarding salt consumption and actual estimated salt consumption, dietary and other health behaviors, and health characteristics including, blood pressure and body mass index.4.
**Objective 4:** To evaluate the accuracy of spot urine sodium as a measure of dietary sodium intake in the Jamaican setting by comparing estimates to 24-hour urinary sodium excretion.

Further details on data sources, sample size and procedures are given in the Methods section.

## Methods

The project will consist of the following components in order to fulfil objectives 1-4 outlined in the Introduction:
1.
**Component 1**: A cross-sectional analysis of data from approximately 1,000 spot urine samples collected as part of the JHLS-III.2.
**Component 2**: A baseline survey of sodium content in commonly consumed foods sold in restaurants chains and individual restaurants.3.
**Component 3:** Conducting a baseline survey of knowledge, attitudes and practices regarding salt consumption and estimation of urinary sodium excretion, dietary and other health behaviors, blood pressure and anthropometry.4.
**Component 4:** Validation study assessing agreement between spot urinary sodium and 24-hour urinary sodium in assessing dietary salt consumption.

Details of each component are described below.

### Component 1: spot urine sodium analyses

*Data sources*

Data from 1,091 spot urine sodium samples, along with relevant sociodemographic and biomedical data were obtained from the third Jamaica Health and Lifestyle Survey (JHLS-III), which was conducted between September 2016 and February 2017.
^
3
^ Some details on the procedures used in JHLS-III have been published.
^
29
^ The survey enrolled a nationally representative sample of Jamaicans 15 years and older using a multi-stage sampling design. In the first stage, 171 enumeration districts (EDs) were randomly selected from a national total of 6,241 EDs, with selection probability proportionate to the size of the ED. In the second stage, 20 households (dwellings) are systematically selected within each ED, using a random starting point. Within each household one individual is selected using the Kish method.
^
31
^ The survey collected data on a wide cross-section of health issues using questionnaires, physical measurements, point-of-care and laboratory measurements and geo-informatics (GIS) mapping. An early morning spot urine sample was collected from study participants and urine sodium measured using the Roche 9180 Electrolyte Analyzer (Mannheim, Germany). These data along with relevant sociodemographic data and data on hypertension and risk factors or comorbidities were obtained from the JHLS-III Research Group. The specific variables included are available as Extended Data. JHLS-III previously received ethical approval from the UWI (Mona) Ethics Committee (ECP 25, 15/16) and the Ministry of Health Ethics Committee (Study Number 2015/51).

*Inclusion and exclusion criteria*

For this component we will include participants from JHLS-III who have available data for urinary sodium. We will exclude participants with missing data on urinary sodium, age, or sex.

*Sample size and power*

Given that we have a fixed available sample size we estimated the power for the 1,091 available urine sodium samples. A design effect for the survey was calculated given the multistage sampling procedure. This was done by calculating the ratio of the variance of the urinary sodium values in samples from JHLS-III with and without accounting for survey design. The estimated design effect was 1.94. Using this design effect our sample of 1,091 participants translates to an effective sample size of 563 participants. Hypothesized mean sodium excretion was obtained from the Health of the Nations Study in Barbados.
^
26
^ Mean sodium intake in that study was 2,656 mg per day. Using the ‘
*power onemean’* command in
Stata (RRID:SCR_012763) and 10% margin of error (
*i.e.*, 2,656 vs. 2,390), the effective sample size of 563 gave a power of 97.5%.

*Statistical analyses*

From these data we will estimate mean dietary sodium consumption and the proportion of patients with high dietary sodium consumption. The PAHO formula will be used to estimate 24-hour urine sodium and potassium.
^
23
^

The PAHO formula uses measured spot urine sodium or potassium divided by measured spot urine creatinine multiplied by estimated 24-hour urine creatinine as shown below.
^
32
^
^,^
^
33
^ The 24-hour urine creatinine was estimated using the Chronic Kidney Disease Epidemiology Collaboration (CKD-EPI) formula.
^
32
^
^,^
^
33
^

Equation 1. PAHO formula for 24-hour urine sodium.

$$\left[\text{Estimated}\;24-\text{hour value}=\left(\text{measured spot urine}\;\mathrm{Na}\;\text{or}\;K÷\text{measured spot urine}\;\mathrm{Cr}\right)\times \text{estimated}\;24-\text{hour urinary}\;\mathrm{Cr}\right].$$

Equation 2. CKD-EPI formula for 24-hour urine creatinine.

$$\left[\text{Estimated}\;24-\text{hour urine}\;\mathrm{Cr}=879.89+12.51\times \text{weight}\;\left(\mathrm{kg}\right)-6.19\times \mathrm{age}+\left(34.51\;\text{if black}\right)-\left(379.42\;\text{if female}\right)\right]$$

Note: PAHO, Pan American Health organization; CKD-EPI, Chronic Kidney Disease Epidemiology Collaboration; Cr, creatinine; BMI, body mass index; Na, sodium; K, potassium.

We will also estimate how dietary sodium consumption vary by sex and other sociodemographic factors, self-reported dietary practices, and biomedical characteristics, including blood pressure levels and hypertension awareness. Multivariable regression models will be used to identify factors associated with high sodium intake. Analyses will be weighted to account for survey design.

### Component 2: salt content of foods sold in restaurants

For this component, the research team will conduct a search to obtain a listing of registered food establishments (defined as serving pre-prepared meals) within Jamaica. All restaurants serving meals that are ready to eat will be eligible for inclusion. A list of such food outlets will be obtained by reviewing listings from the Jamaica Telephone Directory and contacting relevant regulatory organizations responsible for licensing food establishments under Jamaica’s Public Health Act. After compiling the list of food establishments, we will select a sample consisting firstly of restaurant chains, defined as having three or more local branches, then a sample of other restaurants with one or two local branches. This sample of non-chain food establishments will comprise five randomly selected restaurants/cook shops for each of the 60 electoral districts selected for ‘
*Component 3*’ of the study as described below. This will result in a sample of 300 non-chain restaurants. The number of chain restaurants will be determined after we have completed our search for registered food establishments. There is no standard system of restaurant classification in Jamaica. In our analyses we will further define restaurants as fast food restaurants, standard dining in restaurants, and cafes.

Inclusion criteria for this phase of the study will be food establishments that sell ready to eat food items prepared at the site of the restaurant or cookshop. Establishments that sell only packaged food prepared elsewhere will be excluded.

For each selected food establishment, we will contact the restaurant owner or manager initially
*via* telephone and introduce the study and its objectives. The consent form for food establishments can be found as
*Extended data.*
^
41
^ If necessary, an in-person meeting will be arranged. We will seek to obtain a listing of meal items sold in these establishments and information on recipes/ingredient quantities, methods of food preparation and portion sizes to estimate salt content of foods sold by the establishment. We will also seek to obtain information on nutrient content of food sold if these have been previously determined. We will also gather publicly available data on recipes, ingredient quantities, and salt content of meals from restaurant websites and/or social media pages. Where we have difficulty obtaining specific recipes or ingredient quantities, we will estimate salt content based on typical recipes for similar items in the Jamaican context. We will also seek to obtain data from sources such as the US Department of Agriculture Food Central Database international chain restaurants. We will document the extent to which our estimates are based on shared recipes and reported methods of preparation as opposed to estimates made from typical recipes. Foods will again be categorized into groups (
*e.g.*, burgers, fries, chicken preparations, fish preparations, patties, loaves, cooked lunches). The specific food categories with be decided in the analysis stage of the study, guided by the study nutritionist. For each food group, we will estimate mean sodium content per meal and proportion of foods with high salt content. Given that analyses will be purely descriptive, we have not performed sample size or power calculations, but we will report findings based on the available data. We will, however, compute power after the restaurants have been selected in order to assess the probable type 2 error associated with our estimates.

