### Component 3: survey of knowledge, attitudes and practice regarding salt intake and estimation of salt consumption levels

The survey will use a nationally representative sample of 1,200 participants aged 18 years or older. We will approach STATIN to select a total of 60 EDs from all 14 parishes, using probability proportionate to size. Within each ED, we will select 20 households and within each household we will select one individual, using the Kish method.
^
31
^

*Inclusion and exclusion criteria*

We will include non-institutionalized adults, aged 18 years and older, resident in the selected ED. We will exclude institutionalized participants or individuals who are unable to complete the questionnaire due to impaired capacity to understand the questions asked or inability to speak. No other health or social condition were considered as inclusion or exclusion criteria. However, we are collecting data on participants use of medications for hypertension and, specifically, if they are using diuretics. We will assess whether there are differences in urine sodium excretion for those with hypertension or on diuretic therapy. Where necessary we will exclude participants on diuretic therapy from analyses or conduct sensitivity analyses with models excluding and including persons on diuretic therapy.

*Recruitment*

For each selected community we will first obtain a map of the community from STATIN and then arrange a visit to the community to establish the number of households and determine the household sampling interval. We aim to select 20 individuals from each ED, one from each household. The household sampling interval will therefore be determined by dividing the number of households by 20. A visit will be made to each selected household and one person will be selected using the Kish method.
^
31
^ For this procedure, the trained data collectors make a list of all the household members who are eligible to participate in the study, ordered by age and sex and the select one person based on a random number system. If the participant from the selected household refuses to participate we will attempt to recruit a participant from the neighboring household. Recruitment will be supervised by the study’s project coordinator.

*Data collection*

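### Component 2 names the wrong sampling unit, gives 300 restaurants as certain without outlet counts, states no weighting for a fixed take of five, and plans a type 2 error for purely descriptive estimates

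*Protocol article*

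**What the plan says.** **Sampling unit and size.** The section on Component 2 says: "This sample of non-chain food establishments will comprise five randomly selected restaurants/cook shops for each of the 60 electoral districts selected for" Component 3. It continues: "This will result in a sample of 300 non-chain restaurants". The section on Component 3 says: "We will approach STATIN to select a total of 60 EDs from all 14 parishes, using probability proportionate to size". The abbreviation ED is expanded only once, under Component 1 (Data sources), as enumeration district, with 6,241 of them nationally. No electoral districts are selected anywhere in the article.

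**Estimates.** Component 2 plans: "For each food group, we will estimate mean sodium content per meal and proportion of foods with high salt content". Where a restaurant's recipe cannot be obtained, "we will estimate salt content based on typical recipes for similar items in the Jamaican context", and the extent of such filling-in will be documented. Nothing is said about weights. The statistical analysis paragraphs of Components 1 and 3 both say that analyses will be weighted for the survey design.

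**Precision.** The Component 2 analysis is called purely descriptive, and no sample size calculation was made for that reason. The investigators will nevertheless "compute power after the restaurants have been selected in order to assess the probable type 2 error associated with our estimates".

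**The concern.** Three things in Component 2 do not fit together.

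1. The named unit is not the unit that Component 3 selects. The unit matters here because it fixes how many restaurants are available to be drawn.
2. The figure of 300 is given as a result of the design, although it depends on a count that the article does not give. The fixed take of five suits a household survey in which EDs are drawn by size. It does not equalise selection chances for restaurants, and the section does not say how the estimates will allow for that.
3. A type 2 error needs a null value, an alternative and a significance level. Component 2 has none of them, so the planned figure cannot be computed and would not show how precise the estimates are.

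Objective 2, the restaurant sodium estimate, rests on this component. If the number of outlets per ED is not recorded at sampling, weights will be hard to build later.

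**Working it through.** **1. The stated count.** 60 districts × 5 restaurants = 300, which reproduces the protocol's figure. Component 3 gives 60 EDs × 20 households = 1,200, which matches its own target. The 60 in Component 2 can therefore only be the 60 EDs of Component 3. Correcting the name leaves the product unchanged.

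**2. What 300 requires.** Let K_i be the number of eligible non-chain outlets in selected ED i. The sample obtained is the sum over the 60 EDs of min(5, K_i). This equals 300 only if K_i is at least 5 in all 60. The article gives no K_i and no national count. As an assumption, if the average of min(5, K_i) were 1, 2, 3, 4 or 5, the sample would be 60, 120, 180, 240 or 300. Component 4 has a rule for falling short (continue into the next EDs until 120 are reached), and Component 3 replaces a refusing household with a neighbouring one. Component 2 has no such rule.

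**3. Selection chances.** Let M_i be the size of ED i and M the national total, leaving aside any stratification by parish.

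- Chance that ED i is drawn: 60 × M_i / M.
- Household in ED i, if size is the household count: (60 × M_i / M) × (20 / M_i) = 1,200 / M, the same everywhere.
- Restaurant in ED i with K_i of at least 5: (60 × M_i / M) × (5 / K_i) = 300 × M_i / (M × K_i).

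The restaurant's chance is constant only if the outlet count is proportional to ED size, which nothing in the article indicates. Otherwise, among EDs of equal size with at least five outlets, the chance falls in proportion to 1 / K_i. How unequal the chances are cannot be stated without the counts.

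**4. Type 2 error.** Components 1 and 3 each give two means to compare (2,656 against 2,390 mg, and 2,656 against 2,457 mg). Component 2 gives no null value, alternative, significance level or standard deviation, so no power follows from the document.

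**5. What can be computed instead.** The 95% half-width for a proportion p is 1.96 × √(p(1 − p) × D / n), where D is the design effect. With p = 0.5 and n = 300:

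| Assumed D | Effective n | Half-width, proportion | Half-width, mean (1.96/√effective n) |
|---|---|---|---|
| 1.0 | 300 | 5.7 points | 0.11 SD |
| 1.5 | 200 | 6.9 points | 0.14 SD |
| 1.94 | 155 | 7.9 points | 0.16 SD |
| 3.0 | 100 | 9.8 points | 0.20 SD |

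The value 1.94 is the protocol's design effect for urinary sodium and serves here only as an illustration. The other values are assumptions. The table is for a restaurant-level quantity. Half-widths within a food group will differ, because the number of foods per group is not given.

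**The case against.** The strongest reply is that the district name is a slip in expanding an abbreviation. The sentence ties the units to Component 3, so the intended unit can be identified and 300 still follows from 60 × 5. A condensed article may also leave weighting and field rules to a fuller plan. The first part is right: a reader should not infer that a separate sample of electoral districts is planned. The second part has force for weighting, because silence alone would be no finding. But the article does fix the design (EDs by size, five outlets each), states the total without condition, and states weighting for the two components beside it. It is reasonable to ask that Component 2 be completed on the same footing.

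Several stronger readings are not supported:

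- **That the means will be unweighted.** The article does not say so. It says nothing either way.
- **That the sample will fall far short of 300.** This needs outlet counts that the article does not contain. Drawing EDs by size may favour areas with more outlets.
- **That the results will be biased or describe no defined population.** The section gives a list frame and eligibility rules. Bias arises only if sodium content varies with outlet density, which is unknown.
- **That typical-recipe values shrink the standard error by a known factor.** That would require one identical value for all filled-in meals. The section speaks of typical recipes for similar items, so values can differ. It also commits to documenting their extent, and the Discussion names this as a limitation.

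The type 2 error sentence has no comparable defence. It is a stated analysis, not an omitted detail.

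**Conclusion.** The point holds in limited form. Two parts are plain from the text: the unit is misnamed, and the type 2 error calculation is undefined for descriptive estimates without a hypothesis. A third follows by arithmetic: 300 is an upper limit for the non-chain sample, reached only if all 60 EDs have at least five eligible outlets. A fourth follows from the design: selection chances are unequal unless outlets are proportional to ED size, and Component 2 does not say how this is handled.

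Neither the size of any shortfall nor any bias can be derived from the article. The one size that can be given is precision at the full 300: about 5.7 to 9.8 points either side of a 50% restaurant-level proportion, for assumed design effects of 1 to 3. The remedy is worth making now, since the Study status section reports that the restaurant database was still being created.

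**What to change.** 1. Replace the district name in Component 2 with enumeration district.
2. State 300 as a maximum. Give a rule, fixed before sampling, for EDs with fewer than five eligible outlets, for example adding adjoining EDs. If adjoining EDs are used, record which EDs formed each catchment, so that the selection probability can still be calculated.
3. Record the number of eligible non-chain outlets in each sampled ED or catchment from the compiled list. Weight each non-chain restaurant by the inverse of its selection probability. Chains are chosen separately and need their own statement.
4. Delete the power and type 2 error sentence. Report 95% confidence intervals for the food-group means and proportions, allowing for clustering by ED and by restaurant.
5. Show results with and without typical-recipe values as a sensitivity analysis. Do not drop these values from the main estimate, because that would remove the outlets that decline to share recipes and could introduce selection bias.

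The cost is a few sentences, a column of outlet counts and a weighted analysis. The downside is somewhat wider intervals and possibly a smaller stated sample.
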